### Data Collection Methods

#### Patients

At baseline, the following patient characteristics will be collected from the patient records: sex [53], age [53], length in cm, weight at admission in kg [54], BMI in kg/m^2^ [54], WHO performance status [55], American Society of Anesthesiologists Physical Status Classification (ASA PS Classification) [55], use of ≥5 medicaments [56], preoperative diagnosis, tumor type, type of surgery (ie, open, minimally invasive, or robot-assisted), and type of resection. In addition, the risk screening scores (ie, SNAQ, DOS scale, Braden scale, AMEXO, and JHFRAT) will be collected on the day of hospital admission. The number of days spent in the postanesthesia care unit will be collected from the patient records.

Furthermore, socioeconomic data will be collected via a patient questionnaire on the day of admission, including the highest level of formal education, marital status, number of children (≤18 years), and number of live-in children, hours per week of unpaid work and paid work [53]. The degree of social isolation before admission could be a potential confounder, as it is known that socially isolated patients have worse outcomes [57] and will therefore be measured using the Friendship scale [58].

#### Family Caregivers

On the day of admission, baseline characteristics of the family caregivers will be collected using the iVICQ [46]. Background characteristics include sex, age, educational level, relationship between family caregiver and patient, household composition, unpaid and paid work, monthly net household income, and health status.

### Data Management

Patient data will be entered into a web-based data management system (Castor Electronic Data Capture, version 2022.4.1.3), which complies with all applicable laws and regulations. Family caregivers’ data will be entered into an online protected database connected to the app. If family caregivers are unable to enter their data into the app, we will provide written case report forms. Participants are assigned a study number but can be identified in the database by their ID number. The participation identification log will be kept separate from the patient data and will be safeguarded by the principal investigator. For the participating centers, a separate site-specific subject identification log will be kept at each study site.

The integrity of both patients’ and family caregivers’ data will be protected through a variety of mechanisms. Valid rules, range checks, and consistency checks against stored data will be supported. Access to the study data will be restricted, and a password will be used to control access. For the online database, 2-faced authentication is needed for access. Access to the app for family caregivers is password protected, which prevents the user data from being revealed if the device is stolen. Castor data will be stored on certified servers (ISO 27001, ISO 9001, and NEN 7510) as well as app data (ISO 27001 and NEN 7510). Data will also be stored locally in the department’s computer system drive. All hard-copy original study forms will be stored in a secure and accessible place. Files will be stored for 15 years after completion of the study. This study will not be monitored because the potential risk to patients participating in the study is negligible.

### Statistical Methods

#### Overview

Statistical analyses will be performed using the R statistical software package (version 3.6.2; R Foundation for Statistical Computing). Descriptive statistics will be used to summarize the baseline characteristics and process outcomes of the patients and family caregivers. Continuous variables will be presented as means and SDs or medians and IQRs according to the distribution of the variables. Categorical variables will be presented as counts and percentages (%), and numbers and frequencies will be presented for dichotomous data. The distribution of variables will be determined by inspecting histograms and box plots.

The patients’ baseline characteristics of the study arms will be tested for statistically significant differences using the chi-square statistics, Mann-Whitney *U* test, independent samples 2-tailed *t* test, or Fisher exact test. If there are differences between the FIP and treatment groups, we will adjust for confounding variables using multivariate regression analyses.

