### Objectives

Although the results of our pilot study on the FIP were promising, the lack of evidence on the relationship between family involvement and outcomes in patients with gastrointestinal cancer after surgery points to the need for a prospective cohort study. Therefore, the main objective of this study is to evaluate whether FIP for adult patients undergoing oncological gastrointestinal surgery reduces the number of unplanned readmissions compared with usual care. The secondary aims are to evaluate the effect of the FIP on family caregivers by assessing caregiver burden and family caregivers’ well-being and to assess the fidelity of the FIP. Here, we describe the study design and summarize the study protocol, which may also provide practical tools for health care professionals to adopt a more family-centered approach.

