#### Family Caregivers

The eligibility criteria for adult family caregivers are that they are willing and able to deliver fundamental care during hospitalization (for a minimum of 8 hours per day) and after discharge (if needed). Furthermore, they should be nominated as the appointed family caregiver by the patient and should not require support from health care professionals to carry out their own self-care activities. Furthermore, family caregivers will have to be able to read and write the Dutch language and will be included after providing written consent. In this study, family caregivers could be relatives or close friends who know the patient and either live with or are involved in the care of the patient. They are individuals who provide support and with whom the patients have a significant relationship.

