In addition to the effect of the FIP on patient outcomes, we measured the effect of the FIP on family caregiver outcomes, including caregiver burden and well-being up to 90 days after participating in the FIP (Table 1). The Valuation of Informal Care Questionnaire (iVICQ) measures objective burden using the following items: duration and intensity of informal care, patient health, need for permanent surveillance, patients’ living situations, and use of professional care [46]. Subjective burden will be measured using the Caregiver Strain Index plus (CSI+) [47], self-rated burden scale [48], and perseverance time [49]. The well-being of family caregivers will be measured using the Care-related Quality of Life instrument (CarerQoL-7D) and Care-related Quality of Life–Visual Analog Scale (CarerQoL-VAS; Table 1) [50]. Finally, the costs of the FIP will also be measured using the iVICQ [46].

To measure adherence, which is considered a bottom-line measurement of intervention fidelity [51], we will record how many patients are offered the FIP and how many patients decline, including the reasons if they want to disclose. We will use the data recorded by family caregivers to assess the fidelity of the intervention. Up to 5 days after surgery, family caregivers will be asked to record the fundamental and optional care activities they have carried out in the app, and if not completed, to add a reason. The family caregiver registers the activity on the registration form of the app. If multiple family caregivers participate in the FIP, they will all be asked to record the executed activities. Rooming-in of the family caregivers during admission will be checked by ward nurses and researchers (SM, SK, and [name]).

**Table 1 table1:** Outcome variables for patients and their family caregivers.

					T0, baseline		T1, during 5 days after the operation			T2, at discharge		T3, discharge+30 days		T4, discharge+90 days

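### The stated trigger for confounder adjustment covers patients' baseline characteristics only, so no adjustment for caregiver characteristics is planned for the caregiver burden and well-being comparisons

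*Protocol article*

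**What the plan says.** The Objectives make the caregiver comparison an aim of the study: "The secondary aims are to evaluate the effect of the FIP on family caregivers by assessing caregiver burden and family caregivers’ well-being". The Outcomes section under Methods repeats it: "we measured the effect of the FIP on family caregiver outcomes, including caregiver burden and well-being up to 90 days after participating in the FIP".

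Statistical Methods, Overview, then treats the two kinds of participant differently.

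- For description, both are named: "Descriptive statistics will be used to summarize the baseline characteristics and process outcomes of the patients and family caregivers".
- For the comparison of arms, only patients are named: "The patients’ baseline characteristics of the study arms will be tested for statistically significant differences".
- Adjustment depends on that comparison: "If there are differences between the FIP and treatment groups, we will adjust for confounding variables using multivariate regression analyses".

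Statistical Methods, Outcomes, adds univariable and multivariable regression with backward selection, using linear models for continuous secondary outcomes and logistic models for dichotomous ones. It lists no candidate covariates for any outcome.

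Caregiver baseline data are available. Besides the caregiver's age, sex and education, the list in Data Collection Methods, Family Caregivers, covers "relationship between family caregiver and patient, household composition, unpaid and paid work, monthly net household income, and health status". Table 1 also shows a baseline (T0) measurement for the objective burden items, the CSI+, the self-rated burden scale and the CarerQoL, but none for perseverance time.

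**The concern.** The arms are self-chosen. Under Allocation, the caregiver's wishes count alongside the patient's, and a refusal by either one places the pair in usual care. The rooming-in component asks FIP caregivers to be present at least 8 hours a day for the first 5 postoperative days. A caregiver with a full-time job, poor health or young children at home is less likely to agree to that. The same circumstances plausibly affect how heavy caregiving feels afterwards.

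A comparison adjusted only for patient traits could then show no extra burden because freer and fitter caregivers chose the programme. It could also show a difference that the programme did not cause. The first case matters most here, because the Discussion hypothesises fewer readmissions and complications with no increase in caregiver burden. Confounding that lowers apparent burden in the FIP arm would look like support for that hypothesis.

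**Working it through.** **Step 1. Does any stated rule bring caregiver traits into the caregiver models?**

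- *Statistical Methods, Overview:* caregivers appear in the descriptive sentence and are absent from the between-arm test that triggers adjustment.
- *Statistical Methods, Outcomes:* there is a selection procedure but no candidate list, so caregiver traits are neither included nor excluded.
- *Additional Analyses:* the number of caregivers and the optional care activities are examined only as modifiers of patient outcomes. The same subsection says that caregivers, like patients, are analysed in the group chosen before surgery, so a between-arm caregiver contrast is intended.
- *Discussion, Principal Findings:* the call to compare many prognostic variables gives patient examples (perceived social isolation and living status).

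No section states an adjustment for caregiver characteristics.

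**Step 2. How large could the effect be?** The article gives no figure for caregiver imbalance or for the effect of a trait on burden, so there is nothing of its own to reproduce. The inputs below are assumptions.

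- Difference in prevalence of one binary caregiver trait between arms: 20 to 30 percentage points (assumed).
- Effect of that trait on burden: 0.3 to 0.5 SD (assumed).
- Caregivers analysed per arm: 150. This is the patient target in Sample Size, borrowed here.
- Test: two-sided at 5%, as stated in Statistical Methods, Outcomes.
- True effect of the FIP on burden: none.

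Bias = prevalence difference × trait effect.

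- Low: 0.20 × 0.3 = 0.06 SD.
- High: 0.30 × 0.5 = 0.15 SD.

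Standard error of the difference = √(2/150) = 0.115 SD.

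False-positive rate = 1 − Φ(1.96 − bias/SE) + Φ(−1.96 − bias/SE).

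| Imbalance | Trait effect | Bias | False positives, 150 per arm | False positives, 120 per arm |
|---|---|---|---|---|
| 20 points | 0.3 SD | 0.06 SD | 8.1% | 7.5% |
| 20 points | 0.5 SD | 0.10 SD | 13.9% | 12.1% |
| 30 points | 0.3 SD | 0.09 SD | 12.2% | 10.7% |
| 30 points | 0.5 SD | 0.15 SD | 25.5% | 21.3% |

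The 120 column takes the upper end of the article's expected questionnaire loss (150 × 0.8 = 120). Fewer respondents lower the false-positive rate slightly but leave the bias unchanged.

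Over wider assumptions (imbalance 5 to 30 points, trait effect 0.3 to 0.8 SD, 150 per arm), the rate runs from 5.2% to 54.7%. In the opposite direction, a true rise in burden equal to the bias would be cancelled.

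**The case against.** The strongest reply is that the text leaves adjustment open. Backward selection is a second route to a covariate set, its candidate pool is unspecified, and the sentence on adjusting for confounders is not itself limited to patient variables. A reader might infer that caregiver variables are barred from the models, or that the caregiver comparisons will certainly be unadjusted. The document supports neither: it plans no such adjustment, which is different from ruling it out, and an analysis plan that is not shown could supply it.

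A related reply is that a journal article commonly leaves covariate lists to the analysis plan. That would answer a complaint about missing detail. It does not fully answer this point, because the article does state a trigger and words it for patients only, directly after naming both groups for description.

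The mechanism is also open to challenge. The eligibility section asks that caregivers be such that "they are willing and able to deliver fundamental care during hospitalization (for a minimum of 8 hours per day"), without limiting this to the FIP arm. A reader might take the criterion as proof that FIP caregivers alone are selected for time and health. Read literally, it applies to both arms and would narrow the contrast between them. The argument therefore rests mainly on Allocation and the rooming-in section, and no passage says that work, age or household drives the choice.

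Finally, 150 per arm is not a caregiver count. Some patients have no available caregiver, some questionnaires will be lost, and up to three caregivers may take part per patient. The false-positive rates are therefore illustrative only.

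**Conclusion.** The point holds in limited form. Followed as written, the adjustment rule is triggered by patient characteristics alone and nothing else names caregiver covariates, so the caregiver burden and well-being contrasts have no planned adjustment for caregiver traits. Confounding by those traits is plausible because caregivers help choose the arm and the programme demands long daily presence, but this is an inference.

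The illustrated bias of 0.06 to 0.15 SD, with about 8% to 26% false positives, depends wholly on the assumed imbalance and trait effect and on 150 responding caregivers per arm. It shows that the problem could matter, not that it has a known size.

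The primary readmission analysis is untouched. The change is worth making because it protects a stated secondary aim in a non-randomised study and uses data already planned for collection. Dropping significance testing or stepwise selection for the patient variables would not resolve it, since caregiver variables would still not be named.

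**What to change.** In Statistical Methods, Overview and Outcomes, state that all models for caregiver outcomes are adjusted for a prespecified set of caregiver covariates: age, sex, education, health status, paid and unpaid work, relationship to the patient, and household composition. Add the T0 value of the outcome where Table 1 shows one; perseverance time has none, so its model would use the other covariates only. These terms come in addition to the patient covariates and stay in the model whatever the baseline significance tests show.

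Work should enter in the form in which the iVICQ records it, because the caregiver section does not say that hours are collected.

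The cost is a few more model parameters and a rule for missing caregiver baseline data. No new data collection is needed.

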### Study Setting

The study will be conducted at 5 surgical wards that provide care to patients after oncological gastrointestinal surgery in two Dutch tertiary university hospitals in the Netherlands: (1) Amsterdam University Medical Center (UMC), location Academic Medical Center (AMC) and Vrije Universiteit Medical Center, Amsterdam, and (2) University Medical Center Groningen (UMCG), Groningen. The average number of patients undergoing oncological gastrointestinal surgery as treatment for malignant pancreatic, gastric, esophageal, liver, colorectal, or peritoneal tumors in Amsterdam UMC is 415 per year and in UMCG 330 per year. Each participating surgical ward has 25 to 30 beds with a nursing:patient ratio of either 1:4 or 1:5. The participating wards were chosen because health care professionals expressed a willingness to adopt a more family-centered approach to their care.

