### Allocation

Participation in the FIP is based on the preferences of patients and, if available, their family caregivers. This means that when the patients and their relatives want to participate in the program, they will be allocated to the intervention group and when the patients or their relatives do not want to participate in the program (but give consent for observation in the usual care group), they will be allocated to the usual care group. By using this patient preference study design, we might introduce contamination between the intervention and comparison groups, as patients in the comparison group might learn about fundamental care activities and adopt them themselves or receive informal care without the program. Nevertheless, this study design was selected deliberately because no clear signs of contamination were observed between the study groups in the pilot study [16]. To minimize the risk of between-group contamination, the information for patients and their families before inclusion will not include detailed information about the fundamental care activities that comprise the program.

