### Sample Size

The sample size is based on the primary objective of evaluating the effects of the FIP on unplanned readmissions. In our pilot study, we found an absolute reduction of unplanned readmission rates of 15% [16] and considered this 15% reduction of unplanned readmissions as clinically relevant, representing a readmission rate of 20% in the intervention group and 35% in the usual care group. To detect a 15% reduction in readmission rates at a 5% significance level (α) and a power of 80% (1 – β), a sample size of 136 patients per group is necessary, using a continuity-corrected chi-square test. We assume a 10% to 20% loss to follow-up (ie, not completing the questionnaires), and to compensate for this, the total sample size per group will be at least 150. Loss to follow-up is expected owing to the use of repeated questionnaires, which may burden patients. Recruitment ends as soon as both the groups have included 150 patients. To minimize attrition, we will collect detailed contact information and offer patients alternative data collection methods such as paper-based questionnaires if patients do not have an email address [52].

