#### Outcomes

Univariable regression and multivariable regression analyses will be conducted using stepwise backward selection. For the primary outcome (ie, unplanned readmissions up to 30 days after surgery), we will conduct logistic regression analyses. For continuous secondary outcomes, we will use linear regression analyses; for dichotomous outcomes, we will use logistic regression analysis. We will use a general linear mixed model to analyze differences in sleep quality, DOS scores, and AMEXO scores over 5 days after the operation (Table 1). If a difference is observed, a post hoc power analysis will be used to examine which time point differs significantly. A 2-sided *P* value ≤.05 will be considered statistically significant. A 95% CI for the beta coefficient (β) will be calculated.

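### Choosing adjustment variables by baseline significance tests and backward selection can leave real confounders out of the effect estimate in this preference-allocated cohort

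*Protocol article*

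**What the plan says.** Allocation is not random. Under Allocation: "Participation in the FIP is based on the preferences of patients and, if available, their family caregivers". Under Sample Size: "Recruitment ends as soon as both the groups have included 150 patients".

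The Overview of Statistical Methods says that patients' "baseline characteristics of the study arms will be tested for statistically significant differences using the chi-square statistics" or, depending on the variable, a Mann-Whitney, t or Fisher exact test. The consequence follows: "If there are differences between the FIP and treatment groups, we will adjust for confounding variables using multivariate regression analyses". (The comparator there is presumably usual care.)

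The Outcomes part of Statistical Methods adds: "Univariable regression and multivariable regression analyses will be conducted using stepwise backward selection". For the main endpoint: "For the primary outcome (ie, unplanned readmissions up to 30 days after surgery), we will conduct logistic regression analyses". A 95% interval for the coefficient is promised, with no allowance for selection. No retention threshold is given, and no variable is named as always kept.

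The patient part of Data Collection Methods lists a wide range of baseline variables and says of one: "The degree of social isolation before admission could be a potential confounder". The Discussion calls it essential to compare as many prognostic variables as possible between the groups, but names no adjustment set.

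**The concern.** A variable confounds through its link with both group and outcome. Statistical significance of the baseline difference measures neither the strength of the link with outcome nor the bias from omitting the variable; it depends heavily on sample size. A strong predictor of readmission with a moderate, non-significant imbalance is left out under the Overview rule. Backward selection applies a second filter of the same kind, because a real predictor can miss the retention threshold at this number of events. The final interval is then computed as if the model had been fixed in advance.

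In a randomised trial this would matter less. Here, confounder control is what separates a programme effect from differences between families who opt in and those who do not. At stake is the primary conclusion on 30-day unplanned readmissions.

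**Working it through.** **Inputs from the article.** 150 per group; readmission 35% (usual care) and 20% (programme); two-sided alpha 0.05; power 80% (Sample Size, Statistical Methods).

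**The plan's own figure.** Unpooled formula: n = (1.96 + 0.8416)² × (0.35×0.65 + 0.20×0.80) / 0.15² = 7.849 × 0.3875 / 0.0225 = 135.2, so 136 per group. The stated 136 is reproduced, though without the continuity correction that the article names; that is a separate matter.

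**Expected events.** 150×0.35 + 150×0.20 = 52.5 + 30 = 82.5.

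**First filter: does a baseline test flag a real imbalance?** For a standardised mean difference (SMD) d, power ≈ Φ(d×√(150/2) − 1.96).
- d = 0.10: Φ(0.866 − 1.96) = 14%
- d = 0.15: Φ(1.299 − 1.96) = 25%
- d = 0.20: Φ(1.732 − 1.96) = 41%
- d = 0.30: Φ(2.598 − 1.96) = 74%
- Binary factor, 20% v 30%: 52%; 30% v 40%: 44%

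**Second filter: does a real predictor survive elimination?** Wald approximation, overall event rate (0.35+0.20)/2 = 0.275. The information per SD is 300×0.275×0.725 = 59.8. For an assumed log odds ratio of 0.25 per SD, z ≈ 0.25×√59.8 = 1.93. The chance of P<.05 is about Φ(1.93 − 1.96), or roughly one half.

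**Both filters together.** Simulation with 150 per group, true odds ratio 1.00 and 1,500 runs per row. Assumptions not in the article: independent confounders, all placing programme patients at lower risk, and retention at P<.05. Cells give mean OR / false-positive rate.

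| Confounders, OR per SD, SMD | Screening + elimination | Backward from all | All retained |
|---|---|---|---|
| 6, 1.4, 0.10 | 0.88 / 8.2% | 0.96 / 6.0% | 1.00 / 5.5% |
| 6, 1.4, 0.15 | 0.84 / 10.2% | 0.95 / 6.7% | 1.00 / 5.7% |
| 6, 1.4, 0.20 | 0.83 / 11.7% | 0.93 / 8.0% | 1.00 / 5.9% |
| 6, 1.25, 0.20 | 0.85 / 10.7% | 0.90 / 9.0% | 1.00 / 5.2% |
| 6, 1.4, 0.30 | 0.84 / 12.1% | 0.90 / 9.7% | 1.00 / 5.3% |
| 10, 1.25, 0.20 | 0.77 / 17.7% | 0.84 / 12.1% | 1.01 / 5.0% |
| 6, 1.4, 0 (no imbalance) | 1.00 / 5.0% | 1.00 / 5.7% | 1.00 / 5.5% |

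Monte Carlo standard error at 11% is √(0.11×0.89/1500) = 0.8 points.

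A separate simulation added 12 noise variables to 6 same-direction confounders (SMD 0.2, log odds ratio 0.3):
- Unadjusted: 0.71 / 23.1%
- Screening plus elimination at .05: 0.82 / 10.6%
- Backward from all at .05: 0.90 / 7.9%
- Backward from all at .157: 0.95 / 7.3%
- Backward from all at .20: 0.96 / 6.6%

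Variations on the screening route gave 0.91 / 6.9% with only three same-direction confounders, and 0.99 / 5.2% with half of the confounders reversed in direction.

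**Standard errors.** In the confounded rows of the table, model SE divided by empirical SE was 0.90 to 1.00 for screening plus elimination, 0.88 to 0.96 for backward selection from all variables, and 0.96 to 0.98 with everything retained. In the third row, coverage was 88.3% for screening plus elimination and 94.1% with everything retained.

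**The case against.** Several parts of the defence stand.

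- **How the two steps combine is not stated.** The Outcomes text says that multivariable regressions will be run, without condition, so the baseline tests may not gate adjustment. On that reading, backward selection removes most of the confounding, and more of it with a looser threshold. The larger errors belong to the harsher reading only.
- **Direction and size are assumed.** A reader might infer that residual confounding must favour the programme. The article supports a direction for one variable: it says socially isolated patients do worse, and patients without an available caregiver cannot join. For the rest it gives neither direction nor strength, and with mixed directions the mean bias vanished.
- **Interval width.** A reader might infer seriously narrow intervals. The shortfall is about 0% to 12%, part of which also appears with everything retained; most of the lost coverage comes from bias.
- **The retained-set comparator is idealised.** It holds exactly the true confounders. A fixed set with half of them gave 0.83 / 9.7%, no better than the criticised route. The gain depends on choosing the set well.
- **Hospital and ward.** The article states "The study will be conducted at 5 surgical wards", and site is not in its list of patient characteristics. That does not show it will be ignored; a condensed article may leave it to the full plan. Nor is it safe to argue that all listed candidates compete for about 82 events, since screening would remove many first.
- **Partial mitigation exists.** A sensitivity analysis compares programme patients with controls whose caregivers declined. That addresses caregiver availability, but not the other ways in which choosers and decliners differ.

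None of this defends significance as the criterion for confounder control. The article states the method outright, so it is not a detail left to another document.

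**Conclusion.** The concern holds as a badly fixed method: the stated procedure can omit genuine confounders from the primary estimate, and social isolation has no guaranteed place in the model. The chance of missing a 0.2 SD imbalance at baseline is about 59% (100 − 41), which follows from the planned group size alone.

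The consequence for the estimate is conditional. Under moderate same-direction confounding (about six confounders, SMD 0.15 to 0.20, odds ratio 1.25 to 1.4 per SD) and no true effect, expect an odds ratio of about 0.82 to 0.86 and type I error of about 9% to 12% if both filters apply. If only backward selection applies, expect about 0.90 to 0.95 and 7% to 9%. With few or mixed-direction imbalances, the bias is small or absent. The documents do not support saying that the result will be biased, or that it will be biased in favour of the programme.

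**What to change.** Remove the significance trigger and stepwise backward selection from every model that estimates the programme effect. Before the outcome analysis, do one of the following.

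1. Name a confounder set on subject-matter grounds and retain it whatever the P values. For example: age, ASA class or WHO performance status, tumour/resection category, surgical approach, nutritional risk score, Friendship scale, marital/living status, and hospital.
2. Use a propensity-score method built on the pre-surgery variables, and state the target population, since the choice of weights changes it.

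For option 1, collapse categories to suit about 82 events. Six tumour sites (5 parameters), three surgical approaches (2) and one parameter for each of the other six items make 13, or 14 with the programme term: 82.5/14 = 5.9 events per parameter. Collapsing tumour site to three groups and approach to two gives 6 + 2 + 1 = 9, or 10 with the programme term: about 8 per parameter.

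Describe baseline balance with standardised differences instead of P values.

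The cost is a slightly wider interval and a dated, justified change to the analysis plan, since the article reports that follow-up ended in May 2022. The patient variables named are already collected, and hospital is known from the site-specific identification logs.
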